#### Abdominal Drawing in Maneuver (ADIM)

The ADIM is designed to facilitate coactivation of the TrA and LM to stabilize the trunk prior to limb movement [22]. Subjects will receive a traditional training with tactile and verbal instructions in sitting and standing positions before the measurement [22]. To perform ADIM, the participant will be taught to “Take a relaxed breath in and out, hold the breath out, and then draw in the lower abdomen without moving their spine” [20].

#### Contralateral Arm Lift (CAL)

The CAL maneuver attempts to identify the muscular activity of the LM and its size during the execution of the test. With the elbow fully extended and the wrist in a neutral position, the participant will raise the arm to shoulder height. The subject will hold the position for 2 seconds [23].

#### Voluntary pelvic floor contraction

To perform the voluntary PF contraction, the anterior superior iliac spine and the posterior superior iliac spine will be aligned horizontally to avoid the displacement of the base of the bladder. It will be allowed the contraction of the TrA as a synergic muscle. Once the optimum measuring position has been reached, a command will inform the participant to activate the PF: "try to close the urethra as if you wanted to hold back urine". The PF contraction will be maintained for 6–10 seconds [24].

#### Valsalva maneuver

The Valsalva maneuver is a breathing pattern that consists of forced exhalation with the glottis closed to increase the stability of the spine by increasing the intra-abdominal pressure, since the entire abdominal musculature is activated [25]. The sequence given to the subjects to carry out the Valsalva maneuver will be as follows (1)’’ Take the air into the ears with the mouth and nostrils closed”, (2) ’’apply pressure towards the pelvic floor, as if they intended to defecate’’. No instruction shall be given on the contraction or relaxation of the abdominal muscles or the PF. The muscular activity will be recorded within 3 seconds of the participant’s maximum contraction [25].

The maneuvers and its characteristics are summarized in Table 1.

**Table 1 pone.0285441.t001:** Maneouvers and its characteristics.

Maneuver	Verbal command	Muscle contraction	Rest between maneouvers
**ADIM** [22]	Take a relaxed breath in and out, hold the breath out, and then draw in the lower abdomen without moving their spine”	At the end of the exhalation	2 minutes
**CAL** [23]	Raise the extended arm to shoulder height and hold it for two seconds. Then lower it naturally.	2 seconds	2 minutes
**Voluntary PF contraction** [24]	try to close the urethra as if you wanted to hold back urine"	6 seconds -10 seconds	2 minutes
**Valsalva** [25]	’’apply pressure towards the pelvic floor, as if they intended to defecate’	3 seconds	2 minutes

ADIM, Abdominal Drawing in Maneuver; CAL, Contralateral Arm Lift; PF, Pelvic Floor

The methodology of the US evaluations is summarized in Table 2.

**Table 2 pone.0285441.t002:** Methodology of the ultrasound evaluations.

Muscle	Type of probe	Transducer placement	Transducer bandwidth	Caliper placing
LAW (IO, EO, TrA) [26]	Linear	Right abdominal wall at the midpoint between the lower angle of the thoracic cage and the iliac crest. The medial edge of the transducer shall be placed approximately 10 cm from the alba linear.	7’5MHz	Distance [cm) between the superficial and deep border of each muscle belly, which is marked by the hyperechoic fascial lines. The fascial lines will not be included in the measurement.
LM [27]	Linear	L4-L5 facet joint over the articular pillar and the belly of the L4-L5 muscle over the articular pillar and the belly of the ML muscle.	5MHz	Distance (cm) from the most posterior portion of the zygapophyseal joint of L4-L5 and the muscle surface separating it from the subcutaneous cellular tissue
PF [24]	Curved	Suprapubic, just in the mid-sagittal and transabdominal plane. The probe will be tilted caudally and posteriorly to obtain a clear image of the postero-inferior aspect (base) of the bladder, which will vary depending on the bladder fullness of the participants.	2MHz-5MHz	Measure the distance (cm) from the base of the bladder to the central part of the convex probe.
DPH [15]	Curved	Right anterior axillary line, Subcostal. The gallbladder and inferior vena cava will be taken as anatomical landmarks.	2’5MHz -3’5MHz	Distance (cm) from the most distal apex of the right hemidiaphragm to the midpoint of the convex probe coinciding with the hyperechogenic curved line of the diaphragm dome.

LAW, Lateral Abdominal Wall; LM, Lumbar Multifidus; PF, Pelvic Floor; DPH, Diaphragm.

### Data processing

The data will be collected from December 2021 to February 2023. Written informed consent will be obtained from all participants prior to recruitment. The participant Data Collection form that contains information as socio-demographic data (height, weight, and personal medical history) will be completed by the participant and a 10-question questionnaire (S4 Appendix) designed by the research team that will allow the participant to be assigned to the case or control group. The Visual Analog Scale (VAS) [14] as well as the Oswestry Dissability Index scale [17] will be completed only by subjects who have been assigned to the case group. To ensure the authenticity of the data, all individuals will complete the questionnaires independently.

Once the participant has completed all the forms, the customized fixation belt will be placed on the subject, with its corresponding US probes. With the US M-Mode, the start of movement of each specific muscle group will be identified. These results will be compared with the morphological characteristics of each muscle group such as the % of change in thickness of the LM and the LAW, and the endopelvic and respiratory diaphragms excursions.

The US videos and images of each probe will be displayed in four tablets through the USG Wireless program. These tablets are connected to a computer through a customized video capture card.

To objectify the onset muscle contraction of each muscle group, the OBS (Open Broadcaster Software® V.28.1.2 Boston, MA 02110–1301 USA) will be used. The OBS will allow to observe the four videos all at once, where the specific and global muscle contraction can be visualized in a simpler and clearer way. In addition, a stopwatch will be used in the same program to visualize the onset muscle contraction.

The collected data will be saved and imported to a personal laptop for later measurement by a blinded examiner using the program Free software FIJI® V.2.9.0 Cambridge CB3 0HA, UK [28].

### Statistical analysis

The analysis of the assumption of normality will be carried out with the Kolmogorov-Smirnov test with Lilliefors’ correction, as the sample is larger than 50 subjects per group. For the descriptive analysis of the continuous quantitative variables the mean and standard deviation (SD) will be used in the case of meeting the normality and the median and first and third quartiles in the opposite case. In the case of nominal variables, absolute and relative percentage frequencies will be reported. The analysis of the homogeneity of the groups in the demographic variables will be carried out with the t-Student test for independent samples in the case of the continuous variables that comply with the assumption of normality and by means of the Mann-Whitney U test in the case of those that do not. For nominal variables, the Pearson chi-square test will be used or the Fisher exact test if the assumptions for the first one is not met.

The Intraclass Correlation Coefficient (ICC) will be used for the analysis of the intra and inter-reliability of the onset muscular contraction and ultrasound measurements, under the assumption of a mixed model of two factors and absolute agreement, using the average of 3 measurements (ICC3,3) [29]. It will be performed in 20 participants of the sample during standing voluntary pelvic floor contraction maneuver. The presence of a systematic error will be assessed by the statistical significance of the analysis of variance (ANOVA) used for the calculation of the CCI. The standard error of measurement (SEM) will be calculated as the square root of the mean square of the ANOVA error used for the calculation of the JRC, and the minimum detectable difference (MDD) at 95% confidence, using the formula MDD_95_ = SEM * $\sqrt{2}$ * 1.96. The SEM and MDD will also be reported as a percentage of the sample mean. The Bland-Altman agreement charts will then be produced, estimating the agreement limits as the mean difference ± 1.96*DT [30].

For the assessment of compliance with the assumption of homoscedasticity, a visual inspection of the graph will be carried out and the relationship between the differences and the mean values, and between the differences with an absolute value and the mean values, will be analyzed using the Pearson correlation coefficient [31].

For the analysis of the differences between the groups in the continuous quantitative dependent variables that meet the assumption of normality, a mixed 4-by-2-by-2 covariance analysis (ANCOVA) will be used, with the maneuver (ADIM, CAL, Valsalva, voluntary PF contraction) and the position (sitting, standing) as intra-subject factors, the group (pain, healthy) as an inter-subject factor, and the BMI (Body Mass Index) as a covariant. The association between abdominal muscle thicknesses with gender, age, and BMI was examined using Pearson’s correlation coefficient and multiple regression analysis. Compliance with the assumption of sphericity will be assessed with the Mauchly test and that of equality of covariance matrices with the Box test. The partial eta-square coefficient (p2) will be used as an estimator of the size of the ANCOVA main effects and interactions.

It will be performed the Kruskal-Wallis H test for analyze the differences between independent variables (cases and controls) and the onset muscular contraction, as a qualitative ordinal dependent variable. On the other hand, the t-Student test for independent samples with Bonferroni correction will be used for the analysis of post-hoc pairwise comparisons. Cohen’s d (d = 2t / √g) will be used as estimator of the effect size of the post hoc comparisons [31].

If any continuous quantitative dependent variable does not meet the assumptions for carrying out the ANCOVAs, robust analogous methods will be used that do not require compliance with those assumptions, following the procedures described by Wilcox [31]

All analyses will be carried out with the software R Version 4.1.0 (R Core Team (2021). R: A language and environment for statistical computing. R Foundation for Statistical Computing, Vienna, Austria. URL https://www.R-project.org/). An α level of 0.05 with 95% confidence intervals (CI) will be assumed for all analyses.

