## Abstract

Non-specific low back pain represents 90–95% of all cases of low back pain and it has a prevalence of 18% in the adult population, assuming a great socioeconomic impact. The main objective of this observational case-control study study is to evaluate if there are differences in the simultaneous contraction of the core muscles between nonspecific low back pain and healthy subjects. This study will be carried out in the Physiotherapy department of the University of Alcalá. Eighty-two participants <18 years old, will be recruited, paired with NSLBP (n = 41) and healthy (n = 41). The main outcome will be the onset muscle contraction of lateral abdominal wall (internal oblique, external oblique and transversus abdominis), pelvic floor, lumbar multifidus and respiratory diafragm. The maneuvers that the subjects will perform will be abdominal drawing in maneouver, contralateral arm lift, valsalva, and voluntary pelvic floor contraction in sitting and standing. As a secondary objective, to analyze the amount of contraction of each muscle group and the capacity of the diaphragms to be excreted in both groups of subjects. Finally, to relate pain and disability.

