### Sample size calculation

The sample size calculation has been carried out with the program ‘GPower 3.1.5’ and based on the main inter-subject factor of a mixed 4-by-2 analysis of variance (ANOVA). An effect size of 0.25 was estimated, with a correlation between repeated measurements of 0.50, a power of 80% and a level of 0.05. The resulting sample size was 82 subjects.

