**Fig 1 pone.0285441.g001:**
[figure not shown]
Customized fixation belt.

Three of the probes corresponding to the LAW, LM and DPH will be positioned on the right side of the patient as the sound amplifying window offered by the liver is needed to measure the excursion of the DPH [15]. The fourth probe corresponding to the PF is placed transversely and suprapubically on the subject [16]. The probes placement will correspond to the measurement areas of each muscle group that have been previously validated by different authors [15, 16, 19, 20]. The four US images will be visualized and unified in a computer through a video capture card, where the onset muscle contraction and the morphology of the muscles will be analyzed.

An US analysis will be carried out to evaluate the onset muscle contraction of the four core muscle groups in a global and synergic manner, as well as their individual morphological characteristics during the ADIM, CAL, voluntary PF contraction and Valsalva maneuvers in sitting and standing. The measurements will be taken in these two positions since they have been assumed in as possible risk factors for the appearance of NSLBP and its maintenance [21].

The maneuvers and the positions will be randomized by means of opaque envelopes that will be assigned to each patient to eliminate possible biases. All tests will be performed once in sitting and standing positions. with a 2 minutes break between maneuvers. The authors of this study considered that 2 minutes break between each maneuver and 2 minutes of rest between positions, being low intensity tests, could be enough to avoid participant fatigue. All the maneuvers will be taught before each measurement.

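### The planned 8-cell repeated-measures ANCOVA of the continuous ultrasound outcomes normally discards a participant who lacks one single-shot recording; a mixed model would keep the usable data

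*Protocol article*

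**What the plan says.** The Statistical analysis section states that, for continuous outcomes meeting normality, "a mixed 4-by-2-by-2 covariance analysis (ANCOVA) will be used". Manoeuvre (4 levels) and position (2 levels) are the within-subject factors, group is the between-subject factor and BMI is the covariate. Sphericity is to be checked with Mauchly's test and equality of covariance matrices with Box's test. Variables that fail the assumptions go to robust methods. Onset of contraction, the primary outcome, is treated as ordinal and goes to a Kruskal-Wallis test.

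The Procedures section adds: "All tests will be performed once in sitting and standing positions".

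The Sample size calculation section works from the between-group factor of a 4-by-2 mixed ANOVA. Its inputs are: "An effect size of 0.25 was estimated", "with a correlation between repeated measurements of 0.50", "a power of 80% and a level of 0.05". It concludes: "The resulting sample size was 82 subjects". The Abstract plans 41 per group, so the number recruited equals the number calculated.

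**The concern.** Mauchly's and Box's tests belong to the classical repeated-measures model, which works on a full row of within-subject values. Here a full row is 4 × 2 = 8 values per muscle. Each value comes from one recording, so a failed image has no repeat to replace it. The three-measurement reliability study does not help, because it covers 20 participants in one manoeuvre and one position.

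Some failed images are plausible from the protocol's own description: four wireless probes are held by a custom belt, the diaphragm view depends on the liver window, and the bladder image depends on bladder filling. With 8 chances to fail, a small rate per recording becomes a much larger share of incomplete participants, and their valid recordings are discarded too. At stake are precision and power for the six continuous ultrasound variables: thickness change in the three abdominal muscles and the multifidus, and the two excursions. Their analyses could also rest on different subsets of participants.

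**Working it through.** **Inputs from the protocol.** Effect size 0.25 (type not named; read as Cohen's f), correlation ρ = 0.50, α = 0.05, N = 82 in two equal groups, 4 repeated measures in the sample-size calculation, 8 cells in the planned ANCOVA. **Assumed, because the protocol gives no figure:** failure rate p per recording.

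**Step 1: reproduce the 82.** For the between-group effect, λ = f²·N·m / (1 + (m − 1)ρ), tested as F(1, N − 2).

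With m = 4: λ = 0.0625 × 82 × 4 / 2.5 = 8.2, giving power 0.808. Power is 0.803 at 81 and 0.798 at 80. The smallest N with equal groups is 82, so the stated figure reproduces.

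**Step 2: the same inputs with the 8 cells that are analysed.** λ = 0.0625 × 82 × 8 / 4.5 = 9.11, giving power 0.847.

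| Complete participants (m = 8, ρ = 0.5) | Power |
|---|---|
| 82 | 0.847 |
| 74 | 0.808 |
| 73 | 0.802 |
| 72 | 0.797 |

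So 82 − 74 = 8 or 82 − 73 = 9 participants can be lost, about 10 to 11%. The margin depends on ρ. With all 82 complete, power is 0.819 at ρ = 0.55 and 0.792 at ρ = 0.6, where 84 would be needed. The BMI covariate costs one degree of freedom and changes power by about 0.0001.

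**Step 3: complete-case loss.** If failures are independent, the expected number complete is 82 × (1 − p)⁸.

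| Assumed p | Complete of 82 | Power, m = 8, ρ = 0.5 | Power, m = 8, ρ = 0.6 | Power, m = 4, ρ = 0.5 |
|---|---|---|---|---|
| 1% | 75.7 | 0.816 | 0.759 | 0.775 |
| 2% | 69.8 | 0.784 | 0.723 | 0.740 |
| 3% | 64.3 | 0.749 | 0.687 | 0.704 |
| 5% | 54.4 | 0.675 | 0.612 | 0.629 |

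The 8-measure columns match the planned analysis. At ρ = 0.5 the margin is used up at about 1.4% per recording, since 1 − (73/82)^(1/8) = 0.014.

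**Step 4: clustered failures.** Independence is close to the worst case. If failures cluster within participants (beta-binomial with correlation 0.3, an assumption), the same four rates leave about 79, 76, 73 and 67 complete. Power at m = 8, ρ = 0.5 is then 0.83, 0.82, 0.80 and 0.77.

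**Step 5: using all available recordings.** A participant with j usable cells contributes information proportional to j / (1 + (j − 1)ρ). Averaging over j ~ Binomial(8, 1 − p) and dividing by 8/4.5 gives 0.999, 0.997, 0.996 and 0.993 of the full between-group information at the four rates, so power stays at 0.84 to 0.85. This assumes equal correlation between cells; a richer covariance would change the figure somewhat.

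**The case against.** Several points on the other side are sound.

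- **The margin.** A reader might infer that 82 reaches 80% only if nearly everyone is complete. That takes the deletion from the 8-cell analysis and the lack of slack from the 4-measure calculation. For the analysis actually planned, at the stated inputs, about a tenth can be lost. Even on the 4-measure basis, losing two people costs one percentage point.
- **The primary outcome.** A reader might infer that the main comparison loses power. Onset goes to Kruskal-Wallis, which does not need all 8 cells. The loss falls on secondary outcomes.
- **Scope of one failed image.** It removes a participant from that muscle's ANCOVA, not from the study.
- **Selection through BMI.** If failures depend on BMI, a correctly specified comparison that already adjusts for BMI is not biased by them. The documents point to no other selection mechanism.
- **Deletion is inferred.** The article does not say what happens to incomplete participants, and a fuller plan may do so. Participants unable to take the positions or do the manoeuvres are excluded, and videos are saved for later measurement, so one poor frame need not lose a recording.

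What remains is the choice of method. The article fixes a model that, without imputation, cannot use an incomplete participant. That is a stated choice and not an omitted detail, and a better one is available at little cost.

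**Conclusion.** The point holds for the continuous ultrasound secondary outcomes only. The named ANCOVA, as normally run, turns a small failure rate per recording into a larger loss of participants for the muscle concerned. At 8 measures and ρ = 0.5, an independent failure rate of 1% leaves power above 80% (0.816), and 2 to 5% takes it to between 0.784 and 0.675. With clustered failures the fall is smaller, to 0.77 at 5%. If ρ is near 0.6 there is no margin to begin with.

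These sizes rest on assumed failure rates, on reading 0.25 as Cohen's f, and on complete-case deletion as the usual behaviour of the named method. The documents do not support a claim that the study as a whole falls below its stated power, or that the group comparison is biased.

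**What to change.** For the continuous outcomes that would go to the ANCOVA, specify a linear mixed model with the same fixed terms: group, manoeuvre, position, their interactions, and BMI. Fit it by REML with Kenward-Roger degrees of freedom to all available recordings. Pre-specify a covariance that does not impose compound symmetry, because the plan itself treats sphericity as something to check. Participant, participant-by-manoeuvre and participant-by-position random effects would serve, or an unstructured matrix if it converges. Keep the planned robust methods for variables that do not meet the assumptions.

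In the Sample size calculation section, state that 80% power refers to 82 analysable participants on the 4-measure basis.

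The cost is a change of wording, slightly more modelling work and a covariance choice to fix in advance. The model runs in R, the software already planned, and needs no additional data or participants. Its estimates rely on failures depending only on BMI, the other model terms and the recordings that were obtained.

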### Participants

Participants will be chronic NSLBP subjects, and asymptomatic, according to the selection criteria and recruited through non-probability convenience sampling. Participants will contact the University of Alcalá, in Madrid. The participant will be provided with the "Adult Research Patient Information Sheet" (S1 Appendix), an informed consent (S2 Appendix), a ’Participant Data Collection Form’ (S3 Appendix) and the Low Back Pain Questionnaire (S4 Appendix) designed by the research team. Once the subject has signed the Informed Consent form and completed the Data collection form and the Low Back Pain Questionnaire, the inclusion and exclusion criteria will be reviewed by a sub-investigator ([name] or [name]). Finally, the participant will be assigned to the case or control group.

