### Selection criteria

The inclusion criteria for the chronic NSLBP group will be:

Subjects who suffer from chronic NSLBP according to the criteria defined in the scientific literature [1, 2].Participants aged between 18 and 60 years old [12].To have a history of NSLBP at least twelve weeks in the last year [2]Have scored their pain greater than or equal to 3 points out of 10 on a Visual Analog Scale (VAS) [13, 14].

The control group will be subjects asymptomatic, who have neither acute nor chronic low back pain at the time of the measurement, nor who have suffered it in the last year since the day of the visit.

Surgical intervention, vertebral pathology (fractures, cancer, or infection) inability to be in the position or to perform the selected maneuvers will be the criteria for exclusion from this study. Pregnancy will also be a criterion for exclusion [12].

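### Age and sex are left uncontrolled in the case-control comparison: the ANCOVA adjusts for BMI alone and the primary onset test for nothing, and pairing is asserted but never specified

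*Protocol article*

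**What the plan says.** **Recruitment.** Under Participants, cases and controls alike are "recruited through non-probability convenience sampling".

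**Eligibility.** Under Selection criteria, "Participants aged between 18 and 60 years old" stands in the list for the low back pain group. The control definition that follows concerns only freedom from back pain: "The control group will be subjects asymptomatic, who have neither acute nor chronic low back pain at the time of the measurement", and none in the previous year. It gives no age or sex criterion.

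**Abstract.** It reads "Eighty-two participants <18 years old, will be recruited", which conflicts with the Selection criteria, and describes the participants as "paired with NSLBP (n = 41) and healthy (n = 41". No other section mentions pairing or matching.

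**Group model.** Under Statistical analysis, the 4-by-2-by-2 mixed ANCOVA has maneuver and position as within-subject factors, "the group (pain, healthy) as an inter-subject factor, and the BMI (Body Mass Index) as a covariant". The next sentence is a separate item: "The association between abdominal muscle thicknesses with gender, age, and BMI was examined", by Pearson correlation and multiple regression. Group is not mentioned in that analysis.

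**Primary outcome.** Onset, treated as ordinal, is compared between cases and controls by Kruskal-Wallis, with no covariate.

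**Comparability.** Demographic variables are tested for homogeneity between groups. No consequence for the model is stated.

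**The concern.** The study exists to estimate one contrast, pain against healthy, and nothing in recruitment or analysis makes the groups alike in age or sex. If the groups differ on either, and that variable is related to an outcome, part of the observed difference belongs to age or sex and would be read as an effect of back pain.

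The plan already intends to look at gender, age and BMI together as possible correlates of abdominal muscle thickness, yet carries only BMI into the group comparison and gives no reason. The primary outcome has less protection still, since its test ignores even BMI.

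The word used in the Abstract adds a contradiction. If individual pairs are formed, independent-groups tests ignore the design. If none are formed, the reader is led to credit the study with a control for confounding that it does not have.

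**Working it through.** **1. The plan's own sample size.** Inputs from Sample size calculation: f = 0.25, correlation 0.50, power 80%, alpha 0.05, between-subject factor of a 4-by-2 ANOVA (m = 4 measures, 2 groups).

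- Noncentrality: λ = N·f²·m / (1 + (m − 1)ρ) = 82 × 0.0625 × 4 / 2.5 = 8.2, with 1 and 80 df.
- Power is 0.808, and 82 is the smallest even N that reaches 80% (N = 80 gives 0.798).

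The stated 82 reproduces. The point concerns design and model, not arithmetic. For two equal groups, f = 0.25 is d = 0.50.

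**2. Bias from an omitted covariate.** The document gives no age or sex distribution and no correlation with any outcome, so these inputs are assumptions.

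- Bias in outcome SDs = (within-group correlation r) × (group imbalance of the covariate in SDs).
- Examples: r = 0.2 with imbalance 0.25 SD gives 0.05; r = 0.3 with 0.5 SD gives 0.15; r = 0.3 with a 10-year gap and an age SD of 12 gives 0.3 × 10/12 = 0.25.

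**3. False-positive rate with no true group difference.** Two-sided 5% t test, 41 per group, 80 df.

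- One condition: noncentrality = bias × √(41/2).
- Mean of eight conditions, ρ = 0.5, same bias in each: the SD of the mean is √((1 + 7 × 0.5)/8) = 0.75, so noncentrality = (bias/0.75) × √(41/2).

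| Bias (SD) | One condition | Eight-condition mean |
|---|---|---|
| 0 | 5.0% | 5.0% |
| 0.05 | 5.6% | 6.0% |
| 0.10 | 7.3% | 9.2% |
| 0.15 | 10.3% | 14.6% |
| 0.25 | 20.1% | 32.0% |

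A bias of 0.25 SD is half the planned d of 0.50. More extreme inputs go further: imbalance 1.0 SD with r = 0.5 gives a bias of 0.50 SD and 60.9% for one condition.

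**4. Would the homogeneity tests catch it?** Same t test applied to age, 41 per group.

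- Imbalance 0.5 SD: noncentrality 0.5 × √20.5 = 2.26, detected with probability 0.61 and so missed about 39% of the time.
- Imbalance 10/12 = 0.83 SD: noncentrality 3.77, detected with probability 0.96.

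Detection changes nothing in the stated model.

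**5. Power with age, sex and BMI in the model.** λ is multiplied by (1 − R² of group on the covariates) / (1 − R² of outcome on the covariates); error df = 82 − 2 − 3 = 77. The R² values are assumptions.

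| Group membership explained | Outcome explained | Power at N = 82 | N for 80% |
|---|---|---|---|
| 0 | 0 | 0.807 | 82 |
| 5% | 0 | 0.787 | 86 |
| 10% | 0 | 0.765 | 90 |
| 10% | 10% | 0.807 | 82 |
| 0 | 10% | 0.846 | 74 |

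**The case against.** - **No confounding is demonstrated.** A reader might infer that the group differences will be confounded. The document does not support that: it reports no imbalance and no correlation, and the rates above start at 5%. This objection stands.
- **Age and gender are not declared correlates.** It is tempting to read the plan as naming them so. It says only that an association is examined, and only for abdominal muscle thickness. The thickness outcome in the group comparison is percentage change relative to each subject's own resting value, and nothing is said of age or gender in relation to onset or excursion. This stands too; for those outcomes the link is an assumption.
- **Controls need not be younger.** One might suspect that recruitment through a university yields young controls. The article describes a single route for all participants, so a difference between groups is speculation.
- **A large imbalance would be seen.** At 0.83 SD, the planned homogeneity test would flag it about 96% of the time. True, but seeing is not adjusting, and an imbalance of 0.5 SD is missed about 39% of the time.
- **The rates do not describe the primary test.** They apply to a t test or the ANCOVA group effect, and the eight-condition figures need the same bias in every condition. No rate was computed for Kruskal-Wallis. The principle carries over, since a rank test of unadjusted groups has no defence against imbalance, but the percentages should not be quoted for onset.
- **The Abstract's wording may be loose.** The pairing may mean only two equal groups of 41, and the age statement looks like a slip, because participants receive an adult information sheet. Both readings are plausible; each is resolved by correcting the text.

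What survives: the group models are fixed in the article with BMI or nothing, so this is not a detail left to a fuller plan.

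**Conclusion.** The point holds as one of possible, uncontrolled confounding. The text establishes convenience samples, an age criterion listed for cases only, pairing that is claimed without variables, procedure or paired analysis, an ANCOVA adjusted for BMI alone, and an unadjusted test of the primary outcome. It does not establish that age or sex will differ between the groups or that either drives the outcomes.

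The size is therefore conditional. Under assumed biases of 0.05 to 0.25 SD, the false-positive rate of the group effect runs from about 6% to 20% for one condition, or 6% to 32% for the eight-condition mean with ρ = 0.5. It remains at 5% if the groups are balanced. The distortion may be negligible or may equal half the planned effect, and the plan as written cannot remove it in either case. The change is worth making because it is cheap and uses variables already planned for analysis.

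**What to change.** 1. **ANCOVA.** Pre-specify age and sex, with BMI, as covariates in the group model for thickness change and excursion, whatever the homogeneity tests show. Carry the same covariates into the robust alternative.
2. **Onset.** Kruskal-Wallis cannot take covariates, so replace it with an ordinal model that can: for example, proportional odds with group, age, sex and BMI, and a subject random effect if maneuvers and positions are pooled.
3. **Age range.** State one range that applies to both groups, and reconcile the Abstract with the Selection criteria.
4. **Pairing.** Either define the matching variables and procedure and carry them into the analysis (with the pair in the model if individual pairs are formed), or delete the word from the Abstract.

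**Cost.** Two further covariate degrees of freedom, a more demanding model for onset, and some recruitment effort if matching is kept. At N = 82, power falls from 0.808 to about 0.77 if the covariates explain 10% of group membership and none of the outcome (90 subjects would restore 80%). It rises to about 0.85 if they explain 10% of outcome variance and are balanced. The power loss arises only when the groups are imbalanced on the covariates, which is when adjustment may be needed. These figures are for the ANCOVA group effect; the ordinal model was not powered here.
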